## Abstract

**Background:**

Childhood cancer affects and is affected by multiple levels of the social ecology, including social and relational determinants of health (e.g., economic stability, housing, childcare, healthcare access, child and family problems). The 2015 Standards of Psychosocial Care in Pediatric Cancer outline optimal psychosocial care sensitive to these ecological factors, starting with assessment of psychosocial healthcare needs to promote medical and psychosocial outcomes across all children with cancer. To address the first standard of family psychosocial assessment, the Psychosocial Assessment Tool (PAT) is a validated screener ready for broad implementation.

**Method:**

The PAT will be implemented across a national sample of 18 pediatric cancer programs ranging in size (annual new patients) in a mixed methods, comparative effectiveness study, guided by the Interactive Systems Framework for Dissemination and Implementation, comparing two implementation strategies. It is hypothesized that implementation will be more successful at the patient/family, provider, and institutional level when training (strategy I) is combined with implementation expanded resources (strategy II). There are three aims: (1) Refine the two implementation strategies using semi-structured qualitative interviews with 19 stakeholders including parent advocates, providers, pediatric oncology organization representatives, healthcare industry leaders; (2) Compare the two theoretically based and empirically informed strategies to implement the PAT in English and Spanish using a cluster-randomized controlled trial across 18 sites. Stratified by size, sites will be randomized to cohort (3) and strategy (2). Outcomes include adoption and penetration of screening (patient/family), staff job satisfaction/burnout (provider), and cost-effective use of resources consistent with family risk (institution); (3) Based on the results of the trial and feedback from the first and second aim, we will develop and disseminate a web-based PAT Implementation Toolkit.

**Discussion:**

Use of the PAT across children’s cancer programs nationally can achieve the assessment standard and inform equitable delivery of psychosocial care matched to family need for all patients.

**Trial Registration:**

ClinicalTrials.gov, NCT04446728, registered 23 June 2020

Contributions to the literatureFirst study to apply dissemination and implementation methods to psychosocial screening in pediatric populations, specifically children with cancer and their familiesApplication of rigorous implementation methods to pediatric health care settingTest of implementation of psychosocial screening to reduce health disparities

## Background

The diagnosis and treatment of pediatric cancer affects and is affected by multiple levels of the social ecology, including patient and caregiver physical and psychosocial health. Particularly at risk are families with limited instrumental (i.e., financial) and social resources and pre-existing child and family problems. Institute of Medicine Reports [1, 2] and the Standards of Psychosocial Care in Pediatric Cancer [3] call for improvement in delivery of psychosocial care. The standards outline evidence-based care for *all* patients and families to improve health, increase access to care, and reduce health disparities by decreasing distress, addressing risks, and improving quality of life. The first standard is “youth with cancer and their family members should routinely receive systematic assessment of their psychosocial healthcare needs” [4]. Universal screening at diagnosis fosters early identification of psychosocial risks and provides the opportunity to match psychosocial care to the level of family need for more equitable, effective, and integrated services. Confirming this, in qualitative interviews with multidisciplinary healthcare providers regarding the implementation of screening, the overarching theme was that screening all families is important because it facilitates clinical care and partnerships that can improve outcomes especially for those at risk for disparities. However, few programs offer such care in an efficient, comprehensive, consistent manner [5, 6], highlighting critical gaps in care that can magnify health disparities.

This study addresses this critical gap in the delivery of care to our diverse population of children with cancer and their families by evaluating two approaches to implementing an evidence-based, parent report screener of family psychosocial risk in English and Spanish—the Psychosocial Assessment Tool (PAT) [7, 8]. Risk screening initiates a process of preventive interventions across cancer treatment and facilitates access to evidence-based psychosocial care for children, potentially preventing increased distress and long-term limitations to health-related quality of life [9, 10]. Universal, systematic screening assures that assessments are integrated and resources meet the needs of *all* children with cancer and their families. However, barriers to universal, systematic screening and linked evidence-based care have been identified. The Preparing to Implement the Psychosocial Standards–Current Staffing and Services (PIPS-CSS) study of 144 US pediatric cancer programs conducted to prepare for broad implementation of the standards [5, 11] found that there are challenges and inconsistent interpretations of psychosocial care [5, 11]. Similarly, data from the Children’s Oncology Group (COG) [6] and a national survey of social workers [12] demonstrated inconsistent and often inadequate services. Barriers to implementation are evident, and providers note the importance of training in terms of how screening is accomplished [13].

### The Psychosocial Assessment Tool (PAT)

The Psychosocial Assessment Tool (PAT) [7, 8] is an evidence-based parent/caregiver report screener of family psychosocial risk in English and Spanish. The PAT generates a total score and 7 subscales (family structure, social support, child problems, sibling problems, family problems, stress reactions, family beliefs). Since the initial versions of the PAT [14–16], we have refined the PAT with the current all literacy version reflecting the broad assessment of family psychosocial risks. Screening with the PAT can be completed at diagnosis [17], can be used by multidisciplinary staff, and facilitates the delivery of psychosocial care [18]. Embedded in social ecology theory, the PAT total score maps on to the Psychosocial Preventative Health Model (PPPHM, Fig. 1) [19], a three-tier model which represents the distribution of psychosocial risks across the population of families. Most families experience some distress but have minimal risk factors (low levels of distress, few prior child, or family problems) and resources (financial resources, strong social support) that help them cope and adapt to their child’s illness (universal). A smaller group of families (targeted) have identified areas of risk and moderate resources. At the top of the pyramid are families with more severe problems, many risk factors, and few resources (clinical).

**Fig. 1 Fig1:**
[figure not shown]
Pediatric Psychosocial Preventative Health Model

Empirical evidence supports the readiness of the PAT for broad implementation. It is used in 28.9% of pediatric cancer programs in the USA [11] and widely in other countries [20–28]. The PAT is acceptable to families across race, ethnicity, and SES [7, 8, 10, 16, 17, 29] and has been shown to impact psychosocial outcomes at higher levels of distress when results are shared with staff [30]. We adapted the PAT for hematopoietic stem cell transplantation (HCST) [31] including development of a clinical pathway to facilitate its integration in clinical care [32, 33], and in sickle cell disease, adding items to capture relevant aspects of the social context for families (e.g., school absences, changes in housing) [34].

We do not know the extent to which the PAT has been adopted, whether implementation is consistent across families, and if PAT implementation is sustained. The best practices for implementation have not been studied, and barriers and facilitators to systematic implementation have not been evaluated. Challenges such as time, determining who will screen, technical difficulties, and linking screening to care were potential barriers. In a pilot of an implementation model using a workshop and consultation calls in three states, 9 of 12 centers successfully implemented the web-based PAT, half using both the English and Spanish versions [35]. The pilot data informs the implementation and measurement strategies in this study.

### Specific aims

Based on the Interactive Systems Framework for Dissemination and Implementation (ISF) [36], there are three stages in this mixed methods research (Fig. 2). First, two implementation strategies [37], to improve integration of the PAT into standard pediatric cancer care, will be refined using feedback from 19 stakeholders (qualitative methods). The strategies are based on prior PAT studies, the dissemination and implementation literature [37], and Social Ecological [38] and Pediatric Psychosocial Preventative Health Models [19]. Strategy I is training (webinar) to educate providers on the PAT and its administration. Strategy II is Training + Implementation Expanded Resources (TIER), which augments training with consultation calls and identification of a site champion. Second, we will conduct a comparative effectiveness trial of the two strategies at 18 childhood cancer centers of three sizes examining family (penetration, health equity), provider (feasibility, acceptability, burnout, and job satisfaction), and institution (adoption, sustainability, costs) implementation outcomes [39]. We will randomize sites to time of implementation (three cohorts) and strategy (two—I, II). Third, we will develop and disseminate a web-based PAT Implementation Toolkit for family psychosocial risk screening in pediatric cancer.

**Fig. 2 Fig2:**
[figure not shown]
Interactive systems framework and stages of the implementation study

#### Aim 1

Refine strategies I (training) and II (TIER) using semi-structured interviews with stakeholders—parent advocates, multidisciplinary health care providers, national pediatric oncology professional organizations, and health care industry leaders (implementation team).

#### Aim 2

Compare the two theoretically based and empirically informed strategies to implement the PAT in English and Spanish using a cluster-randomized controlled trial. Compared to training:

**H2.1**. At the patient/family level, TIER will be associated with: (a) a higher proportion of families of newly diagnosed children screened and provided with feedback (penetration) and (b) higher rates of screening for ethnic minority and socioeconomically diverse families (health equity).

**H2.2**. At the provider level, TIER will be (a) more feasible and rated as appropriate and acceptable, (b) associated with greater engagement in addressing health disparities, and (c) associated with less burnout and better job satisfaction.

**H2.3**. At the institution level, TIER will be associated with: (a) a higher rate of site participation (adoption), (b) more positive perceptions of implementation benefits and fewer challenges (sustainability), and (c) psychosocial care better matched to need demonstrating a more equitable distribution of services and costs of care.

#### Aim 3

Based on the results of the trial and further guidance from the implementation team, we will integrate acceptable, feasible, and effective strategies to develop and disseminate a web-based PAT Implementation Toolkit.

## Methods and design

### Overview of the study

The aim of this mixed methods research is to implement universal, systematic family psychosocial risk screening with the PAT in English and Spanish to assure that *all* families of children newly diagnosed with cancer at the participating cancer centers are screened. The setting/context of the research is pediatric cancer programs in the USA. The approach, reflected in the three aims, is guided by the ISF [36]. We selected specific implementation strategies from the Expert Recommendations for Implementing Change (ERIC) project [37] targeting implementation outcomes at three levels (patient/family, provider, institution). ERIC strategies utilized are noted in parentheses throughout this article.

Aim 1 corresponds to the first component of the ISF, Prevention Synthesis and Translation System. We will prepare programs to implement the PAT by conducting qualitative semi-structured interviews with a diverse set of stakeholders (*n* = 19). Interviews will be focused on details of strategy I (training via webinar) and strategy II (training + TIER—consultation calls and identification of a champion), followed by questions about facilitators and barriers, and about implementation strategies and resources needed for universal screening and care delivery to address health inequities. We anticipate fine-tuning and adding components to improve penetration and health equity targets, acceptability and feasibility, adoption, and sustainability.

The activities of aim 2 correspond to the second component of the ISF, Prevention Support System. Support for those implementing innovation occurs at multiple levels within the system—*patients/families, providers,* and *institution.* To implement the PAT in English and Spanish, 18 pediatric cancer programs, of varying sizes and with geographic distribution assuring representation of ethnic and racial minority families and families at socioeconomic risk, have agreed to participate. We will conduct a cluster-randomized comparative effectiveness trial of the two implementation strategies across three cohorts stratified by size of site based on new patients per year (Fig. 3).

**Fig. 3 Fig3:**
[figure not shown]
Study flow diagram

Aim 3 activities correspond to the third component of the ISF, Prevention Delivery System, in the development and dissemination of the PAT Implementation Toolkit.

### Stakeholder interviews to refine implementation strategies (aim 1)

Qualitative interviews will be conducted with a national group of diverse stakeholders, selected using purposive criterion-based sampling [40] to represent different levels of the social ecology. The data from the interviews will inform components of the two implementation strategies and incorporate questions related to broader implementation (e.g., facilitators and barriers). The stakeholder interviews focus on ERIC implementation strategies (use advisory boards and workgroups, prepare patients/consumers to be active participants, and build a coalition).

#### Participants

Participants (*n* = 19) are parent advocates, multidisciplinary healthcare providers, members/leaders of key pediatric oncology professional organizations, and leaders in the pediatric healthcare industry.

#### Procedure

Each stakeholder will be interviewed by video conference using a theoretically driven and empirically based semi-structured interview guide [41]. The purpose of the interview is to refine strategies I and II, identify additional barriers or facilitators of implementation across the patient/family, provider, and institution levels, and ensure PAT implementation strategies address these barriers to reduce disparities in care.

### Cluster-randomized comparative effectiveness trial (aim 2)

PAT implementation will be tested using a head-to-head randomized implementation (comparative effectiveness of two implementation strategies) trial initiated in three cohorts of 1 year each (2021, 2022, 2023). All 18 pediatric cancer programs invited to participate in the trial agreed to a 2-step randomization process stratified by size of site; sites will be randomized to one of three cohorts and then to strategy, comparing strategy I (training) with strategy II (TIER).

#### Selection of sites

The following criteria were used in site selection:
*Provide staff and tablet computer for screening*. Each site agreed to provide the staff person(s) screening and tablets. Each site will be provided support for a portion of the site PI’s effort and a part-time research coordinator based on center size for purposes of research only (the research coordinator will not do the screening).*Center size*. Because program size is related to the size of the psychosocial team and related psychosocial resources [5], we used PIPS-CSS data to stratify by size to obtain three equal and clinically relevant groups based on number of new pediatric cancer patients annually—small (30–60), medium (61–149), and large (150+). We selected 6 sites for each of the three size categories.*Psychosocial staff*. To assure that there are staff to conduct screening and act on the results of screening, selected sites are at or above the median for the size of their psychosocial team (number [full time equivalents] social workers + psychologists + psychiatrists + child life specialists) [5] based on PIPS-CSS data.*Diversity of population*. We selected centers in states with a high percentage of ethnic or racial minority families and/or families with socioeconomic disadvantage. CA, TX, FL, NY, and NJ have large Hispanic populations [42]. AL, NC, and VA have the most rapidly increasing Hispanic populations, and AL, LA, NC, and VA have the largest percentage of African-Americans [43]. Thirteen out of 18 sites are in these states. Twelve out of 18 are in states with > 20% of children living in poverty [44]. Other sites were selected to balance geography, race, ethnicity, and SES.

#### Participants

Since screening will be integrated into the clinical services of the centers, it will be routine clinical care. Coded EHR data with minimal protected health information (PHI) will be collected for patients. Reflecting the importance of staff in implementation [45], consented participants include the site PI and screeners and, in strategy II, the champion.

#### Procedure

All sites, regardless of randomization to strategy I or II, will participate in a 3-h professionally prepared webinar (develop educational materials, distribute educational materials) at the beginning of their cohort year. The webinar will include all information necessary to understand, access, and deliver the web-based PAT. The webinar will be based on our in-person training program and curriculum [35] modified to integrate feedback from aim 1 interviews. Each site PI, all screeners, and the research coordinator will participate. For sites randomized to strategy II, the champion will attend. We will work with sites to identify this team and the champion (in TIER) “individuals who dedicate themselves to supporting, marketing, and driving through an implementation, overcoming indifference or resistance that the intervention may encounter in an organization” [37].

After the PAT is completed online, it is scored immediately, and a summary of the score and clinical concerns identified is generated. Only coded data will be transmitted to the study data core. A master list for this data will be maintained at each respective study site and will not be shared with the core research team. We will provide support to sites in the technical aspects of the implementation related to using the web-based forms (centralize technical assistance). If we identify any pattern of problems with technical aspects of implementation, we will communicate with sites promptly.

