#### Measurement/outcomes (all sites)

The measures assess outcomes across patient/family, provider, and institution levels (Table 1) that are clearly operationalized and reproducible [46]. Site PIs and coordinators will attend training on data collection procedures, in separate sessions for the two conditions.

**Table 1 Tab1:** Measurement

Level/Hyp	Concept	Source	Metric/measure
Patient/family 2.1	Penetration Health equity	EHR (monthly)	Demographics: race, ethnicity, zip code, insurance No. eligible families, English/Spanish No. eligible families screened, English/Spanish % Family feedback letter provided
Provider 2.2	Feasibility Appropriateness Acceptability Engagement in addressing health disparities Job satisfaction Burnout	Survey (Pre, 6-month, Post)	Acceptability of intervention measure Intervention appropriateness measure Feasibility of intervention measure AREA scale of physician engagement Satisfaction employees healthcare Maslach Burnout Inventory version for Medical Personnel
Institution 2.3	Adoption Sustainability: perceived benefit Cost-effectiveness: services/need and cost	Survey	Site participation rate PAT implementation questionnaire
		EHR (monthly)	Psychosocial Services and Medical Treatment Checklist Intensity of Treatment Rating Scale

At the patient/family level (Hyp 2.1) the site coordinator will extract EHR data and send the coded data via REDCap to the data core. The following data for English and Spanish versions of the PAT will be reported monthly: new patients meeting eligibility requirements per the PAT implementation plan; patients with documentation of PAT screening; patients receiving feedback letter; demographic data on all eligible and all screened (race, ethnicity, zip code, insurance).

At the provider level (Hyp 2.2), the site PI and screeners will complete the following self-report measures (~ 15 min) at baseline (T1), and 6 (T2) and 12 (T3) months via REDCap: acceptability of intervention measure; intervention appropriateness measure and feasibility of intervention measure [47]; measure of physician engagement in addressing racial and ethnic health care disparities [48], satisfaction of employees in healthcare survey [49], and Maslach Burnout Inventory [50].

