The outcomes at the institution level (Hyp 2.3) are as follows: adoption, the intention of sites to use the PAT (the ratio of sites that initiate the study); whether screening is perceived as an asset to the institution using the PAT Implementation Questionnaire (PIQ) [35] which will be completed by the site PI, the screeners, and the champion at T1, T2, and T3; whether services are matched to the needs of families based on PPPHM levels using EHR data using the Psychosocial Services and Medical Treatment Checklist (PSMTC) [18] at 30, 60, and 90 days; cost using the data from the PSMTC to estimate the amount of psychosocial staff time and national median hourly salary data [51–53]. The Intensity of Treatment Rating Scale (ITR-3) [54] will be completed at the 90-day post-screening data collection time point based on diagnosis, stage, and treatment.

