PAT implementation will be tested using a head-to-head randomized implementation (comparative effectiveness of two implementation strategies) trial in three cohorts over 3 years. *Randomization*. Eighteen sites will be randomized to one of three cohorts. Each cohort will be further randomized to one of the two strategy conditions. Randomization will stratify sites by size to maximize internal validity and statistical power. Sites will be randomized by a data analyst not connected with the study using a two-step Excel = RAND() function. The sequence will be stored in a password-protected electronic file. *Sample size*. The estimated sample of patients/families is based on the median number of new patients each year from the PIPS-CSS database: small (*n* = 60), medium (*n* = 92), large (*n* = 339) multiplied by 6 sites at each size, a total of 2946, with 1473 families allocated to each strategy. With an anticipated Interclass Correlation Coefficient (ICC) [65] of .005, the effective sample size is 950 per arm, a sample size that is sufficient to detect a small effect between the two strategies given 80% power (alpha = .05, one sided). We project a Hispanic sample of 20% of the total (*n* = 589). Based on our research [8], approximately 30% of Hispanic caregivers will be more acculturated/not literate in Spanish at the level necessary to complete the Spanish PAT, rendering a sample of 412. With an anticipated ICC of .005, the effective sample size is 224 which is sufficient to detect a medium effective between the English and Spanish versions given 80% power (alpha = .05, one sided). At the provider level, each of 18 sites has a PI and up to four people screening, and for TIER sites, a champion. Therefore the staff sample ranges from a minimum of 45 ([18 × 2] + 9) to a maximum of 99 ([18 × 5] + 9), likely in the middle given the range of size of sites. At the institution level, 18 sites will be randomly assigned to one of two strategies (9 sites/group). These sample sizes are comparable to other implementation science studies [66].

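### Nothing fixes the staff who rate H2.2 and the PIQ before strategy is disclosed, so raters can be selected differently by arm, and champions rate the PIQ in TIER only

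*Protocol article*

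**What the plan says.** All references are to the protocol article.

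- **Selection of sites.** Sites committed to staff the screening, but no individuals are named: "Each site agreed to provide the staff person(s) screening and tablets".
- **Cluster-randomized trial (aim 2), opening paragraph.** On order, "sites will be randomized to one of three cohorts and then to strategy". No date is given for naming screeners relative to either step.
- **Procedure (aim 2).** The webinar is for the PI, the screeners and the coordinator. It then adds "For sites randomized to strategy II, the champion will attend", and continues "We will work with sites to identify this team and the champion (in TIER").
- **Strategy I and Strategy II.** Creating implementation teams is listed under Strategy I. In Strategy II the PI and the screening staff also join a one-hour consultation call each month.
- **Participants (aim 2).** On consent, "consented participants include the site PI and screeners and, in strategy II, the champion".
- **Measurement/outcomes.** For H2.2, "the site PI and screeners will complete the following self-report measures" at T1, T2 and T3. For the PIQ, the wording is "which will be completed by the site PI, the screeners, and the champion at T1, T2, and T3".
- **Data analysis, Aim 2.** On staff numbers, "each of 18 sites has a PI and up to four people screening", plus a champion at TIER sites. H2.2 is compared by two-group SEM, with latent growth curves for time. The PIQ (H2.3b) is compared by ANOVA, and no baseline adjustment is stated.

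**The concern.** Randomising sites balances the sites. It does not balance individuals recruited within sites after allocation is known. Here those individuals are the measuring instrument: feasibility, acceptability, engagement, burnout, job satisfaction and the PIQ are all personal ratings from a handful of staff per site.

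The role being filled differs by arm. A TIER screener accepts a monthly call and a Training screener does not. A site that knows its strategy when it picks screeners could put forward people with more time or more interest, and the study team takes part in the choice. A between-arm difference in ratings could then partly reflect who was asked.

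The PIQ has a second problem that needs no inference. Champions exist only in TIER and rate the PIQ there, so the ANOVA compares PIs, screeners and champions with PIs and screeners. The Strategy II section expects the champion to be an enthusiastic and committed clinical leader, which is a plausible source of more favourable PIQ ratings.

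**Working it through.** **1. The protocol's own count.** With a PI and 1 to 4 screeners at each of 18 sites, plus 9 champions:
- minimum: 18 × 2 + 9 = 45
- maximum: 18 × 5 + 9 = 99

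Both match the stated figures.

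**2. Raters by arm.** There are 9 sites per arm, and s is the number of screeners per site.

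| | s = 1 | s = 4 |
|---|---|---|
| Training, PI + screeners: 9(1+s) | 18 | 45 |
| TIER, PI + screeners: 9(1+s) | 18 | 45 |
| TIER with champions: 9(1+s) + 9 | 27 | 54 |
| Screener share of H2.2 raters: s/(1+s) | 50% | 80% |
| Champion share of TIER PIQ raters | 9/27 = 33% | 9/54 = 17% |
| Champion share of Training PIQ raters | 0 | 0 |

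The H2.2 rows count PIs and screeners only, as the measurement section lists them. Like the protocol's own count, the table treats the champion as an additional person.

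**3. Screener selection, one respondent per TIER site (assumed shift).** The shift in the TIER H2.2 mean is the individual shift divided by raters per site.
- 0.5 SD: 0.5/5 = 0.10 SD to 0.5/2 = 0.25 SD
- 0.3 to 0.8 SD: 0.3/5 = 0.06 SD to 0.8/2 = 0.40 SD

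For scale, the smallest difference detectable with 80% power at one-sided 0.05, ignoring clustering, is 2.486 × √(2/n) per arm. The one-sided 0.05 is borrowed from the patient-level sample size, since no provider-level power is stated.
- n = 45: 2.486 × √(2/45) = 0.52 SD
- n = 18: 2.486 × √(2/18) = 0.83 SD

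The 0.5 SD case is therefore 0.10/0.52 = 19% to 0.25/0.83 = 30% of the detectable difference.

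**4. Screener selection, all TIER screeners (assumed shift).** With no true effect, bias b = shift × s/(1+s), SE = √(2/n), and the chance of falsely favouring TIER is Φ(b/SE − 1.645).

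| Assumed shift | b, s = 1 | Chance, s = 1 | b, s = 4 | Chance, s = 4 |
|---|---|---|---|---|
| 0.2 SD | 0.10 | 0.09 | 0.16 | 0.19 |
| 0.3 SD | 0.15 | 0.12 | 0.24 | 0.31 |
| 0.5 SD | 0.25 | 0.19 | 0.40 | 0.60 |

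The nominal rate is 0.05. Clustering is ignored; allowing for it would widen the SE and lower these chances.

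**5. Champions and the PIQ.** If champions rated 0.5 SD more favourably (assumed), the TIER PIQ mean would rise by 0.5 × 9/27 = 0.17 SD (s = 1) or 0.5 × 9/54 = 0.08 SD (s = 4), with no selection of screeners at all.

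**The case against.** The strongest reply is that the timing for screeners is inferred. Only the champion's identification must follow allocation. A sentence that mentions both does not date the naming of screeners, and a condensed article may leave that date to the full protocol. This stands as a limit on the claim. Still, the sentence follows one about sites already randomized, team creation is listed under an allocated strategy, and nothing in the article points the other way.

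A reader might go further and infer that the arms do compare differently selected staff, or that the bias favours TIER. The article supports neither. The same identification step covers sites in both arms, no selection criterion differs by arm, and those surveyed are the people doing the screening. What differs is the job, because of the monthly calls. That gives a mechanism but does not show that selection took place.

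It is also fair to say that T1 ratings and growth curves offer some protection. A stable difference in level would show at T1, and comparing change would remove it. They would not remove differential change among more motivated staff, and the PIQ ANOVA states no use of T1. So one cannot say that no model could correct the bias, only that the stated models may not do so fully.

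Finally, one might regard site PIs as a safe comparison because they predate allocation. No section says so, and the team to be identified, as listed in the Procedure section, includes the PI.

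**Conclusion.** The concern holds as an unprotected risk of selecting raters after allocation, together with one definite imbalance.

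- **Certain:** champions are 17% to 33% of TIER PIQ raters and 0% of Training raters, so H2.3b as described compares different mixes of rater. How far this moves the result depends on how champions rate, which is unknown.
- **Inferred:** screeners are identified with the strategy known. The Procedure section reads that way and no section rules it out.
- **Not given:** the size and direction of any screener selection. The H2.2 shift of 0.06 to 0.40 SD rests on an assumed 0.3 to 0.8 SD difference in one respondent per TIER site and none in Training. The false-positive rates rest on the stronger assumption that all TIER screeners shift.

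The case for acting is that screeners are half to four-fifths of the H2.2 raters and that the protection costs almost nothing. Observed bias is not part of that case. If the full protocol already fixes the roster before disclosure, the screener part is answered and the champion part remains.

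**What to change.** 1. Have every site name its PI and screeners in writing before its strategy is disclosed. Identify the TIER champion only after that list is locked.
2. Define the primary between-arm H2.2 and PIQ comparisons on those named PIs and screeners. Report champion PIQ ratings separately, as a description of TIER.
3. Include screeners who join later as replacements only in a sensitivity analysis.
4. Add a PI-only sensitivity analysis, restricted to PIs documented as in place before allocation. Without that documentation it does not address the problem.

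The cost is one short form per site and a sentence or two in the analysis section. The downside is small: staff turnover may slightly reduce the primary rater set, and the sensitivity analysis with replacements shows whether that matters.
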